#### Intervention group

Participants assigned to the intervention group will perform the SEP as a home program. Additionally this group will receive six to ten session of individualized physiotherapy (IP), based on the findings of the clinical examination and the individual main complaints of the patient. To guarantee a uniform decision making process and to deliver a defined and repeatable way of treatment application a decision tree was developed. The decision tree was previously tested in patients with SIS to improve weaknesses and to test its practicability. It consists of three parts and directs initial treatment applications. The first part of the decision tree addresses predictive signs for a poor treatment outcome such as recurrent episodes of shoulder pain in the past [7,9,11,12], severe pain or long duration of the current episode [82-84], signs indicating a tear of the rotator cuff [85,86], and restriction of external rotation and/or elevation of the shoulder [9,87].

The second part leads the therapist through factors maintaining or contributing to the patients' problem such as general posture, ADL's, working activities and work place setting, leisure and sports activities, and patients' understanding of his problem. The third part guides through the positive findings of the physical examination of the upper quarter (cervical and upper thoracic spine, shoulder and shoulder girdle). Local factors will be treated according to the manual therapy concepts of Maitland [57], Kaltenborn [88], Evjenth and Hamberg [56], or Butler [61].

For further treatment decisions and as an important part of treatment application a defined clinical reassessment process is implemented, adapted from Jones and Rivett [89]. The reassessment process, based on the test-retest-principle, delivers important information about the effect of an applied intervention or technique and thus assists the therapist in further decision making.

#### Main contrast between both groups

The main difference between both groups is that the intervention group additionally receives individualized physiotherapy considering all predictive, local or contributing factors that may maintain or contribute to the patients' problem, identified through clinical examination. Therefore this intervention, combining a shoulder specific exercise programme with a defined decision making process and clinical experience, represents a best practice approach.

### Outcome measures

Selection criteria for the outcome measures used in this study were their reliability and validity in relation to the study population, and also their sensitivity to detect change statistically, whether it is relevant to the patient or clinician or not. Another important criterion was their practical applicability in a clinical setting. The main focus is on pain and functioning. Primary outcome measures will be as follows:

#### 1. Shoulder Pain and Disability Index (SPADI)

The SPADI is a shoulder specific self-reported questionnaire measuring pain and disability in patients with shoulder pain of musculoskeletal origin [90]. It contains 5 items assessing pain and 8 items assessing shoulder function and is easily applicable in daily practice. Each item is scored on a 100 mm visual analogue scale (VAS); the right end of the VAS is defined as "worst pain imaginable/so difficult required help", the left end as "no pain/no difficulty". A score is then calculated out of 100 with higher scores reflecting higher pain/disability levels. The SPADI has shown to be valid and highly responsive in assessing shoulder pain and function [90,91]; it is therefore highly recommended for the use in patients with SIS [92]. The German version of the SPADI also showed an excellent reliability and internal consistency for both, total score and sub-scores. A minimum improvement in the total SPADI score of 11 points will be considered as a minimum clinically important change [93].

#### 2. Patients' global impression of change (PGIC)

Measuring PGIC is a clinically relevant and stable concept for interpreting truly meaningful improvements in pain from the individual perspective [94,95]. It is measured with the help of an ordinal scale with 1-much worsened, 2-slightly worsened, 3-unchanged, 4-slightly better, 5-much better, whereas a rating of "slightly better" will be defined a priori as a clinically important and meaningful difference and therefore as a successful result. According to this definition, the scale is then dichotomized. To test stability of this dichotomization a sensitivity analysis will be conducted.

Secondary outcome measures will be:

#### 1. Generic Patient-Specific Scale (GPSS)

The GPSS is published by Stratford et al. [96] and assesses individual complaints and restrictions in a short and efficient way. It is based on the patient-centred approach, identifying the most problematic areas of functioning.

The GPSS is a reliable and valid tool and also sensitive to detect change over time [97]. Although it is a generic outcome measure, its validity, reliability and sensitivity has been established for different patient groups [96,98,99]. For this study, patients will chose 3 activities they got difficulties with and rate the ability to perform them on an 11-point visual numeric rating scale (VNRS). 10 at the right end of the VNRS is defined as "I can do the chosen function without difficulty", 0 at the left end as "I am unable to do the chosen function". An average score across all activities is calculated. Because the expected change of severely restricted activities is less than the expected change of only mild restrictions, a minimum change of 30% will be considered as a clinically important improvement [95,100].

#### 2. Average weekly pain score

Patients will rate their average weekly pain intensity on an 11-point VNRS. The VNRS is a one-dimensional measure to assess pain intensity. The distance between each number is 10 millimetres; 0 on the left end of the VNRS is defined as "no pain at all", 10 at the right end as "as much pain as I can imagine". An improvement in pain level of 2 points or more was defined as a clinically important and meaningful difference [95,100].

#### 3. Patient satisfaction with treatment

After 5 weeks all patients will rate their satisfaction with treatment on an 11-point visual numeric rating scale (VNRS). 10 at the right end of the VNRS is defined as "completely satisfied", 0 at the left end as "completely dissatisfied".

#### 4. Fear Avoidance Beliefs Questionnaire (FABQ)

It has been shown that fear of movement is an important obstacle to a successful rehabilitation in patients suffering from low back pain. To be able to analyze the influence of fear of movement on treatment outcome in patients with SIS, a modified version of the FABQ is used in this study. The FABQ was developed by Waddell et al. [101] to assess the influence of patients beliefs about physical activity and work on low back pain. The German version of the FABQ shows good psychometric properties and is therefore used in this study [102-105]. The FABQ is a 16-items questionnaire. Each item is scored on a seven-point Likert scale (0 = strongly disagree, 6 = strongly agree). A total score is calculated by summing up the resultant scores. Sub-scores for physical activity and work are calculated, with 7 items assessing beliefs about work (item 6, 7, 9, 10, 11, 12, 15) and 4 items assessing beliefs about physical activity (item 2, 3, 4, 5). Higher scores reflect a higher presence of fear avoidance believes.

#### 5. Pain Catastrophizing Scale (PCS)

Besides fear of movement, catastrophizing may also play an important role in mediating responses to pain, leading to perception of higher pain intensities and therefore influencing treatment outcome negatively [106-108]. The PCS is a multidimensional, reliable and valid 13-item self report measurement tool with a strong association to pain and emotional distress [106,107,109,110]. The PCS has been validated for the German population [111]. It comprises three subscales for rumination (item 8 to 11), magnification (item 6 to 7, 13), and helplessness (item 1 to 5, 12). Each item is rated on a 5-point scale from 0 (not at all) to 4 (all the time). A total score and sub-scores for each subscale are calculated by summing up the ratings for each item within a subscale. In a sample of 86 patients with sustained soft tissue injuries to the neck, shoulders or back including shoulder patients, Sullivan et al. [112] found that catastrophizing was significantly correlated with patients' reported pain intensity, disability and employment status. The rumination subscale was the strongest predictor of pain and disability. Due to a sufficient test-retest stability even over a longer period of time the PCS is a appropriate screening tool for pain catastrophizing [113].

#### 6. Patients' expectancies of treatment outcome

Patients' beliefs about the success of a given treatment may influence treatment outcome; this has been shown by Goossens et al. [114] and Smeets et al. [115] in low back pain patients. For this trial a modified question of the Credibility/Expectancy Questionnaire (CEQ), developed by Deviliya and Borkovecb [116], to measure patients' expectancies is used. The CEQ shows high internal consistency and good test-retest reliability. The question is: "By the end of the therapy period, how much improvement in your limitations due to shoulder pain do you think will occur? The question is scored on an 11-point visual numeric rating scale (VNRS) from 0 (no improvement) to 10 (completely recovered). A higher score will reflect more positive expectancies.

#### 7. Compliance with treatment, direct (health care) and indirect (non-health care) costs

A shoulder log book will be used to obtain the following data: i) Compliance of participants with treatment including the attended treatment visits out of a maximum of ten and the performance of the given home exercises; ii) direct health care costs including physiotherapy, other health provider visits, diagnostic tests, prescriptions and over the counter medication due to shoulder complaints; iii) indirect health care costs including days of sick leave and paid help. The log book is presented in booklet form containing instructions and explanations about the objective of the log book. Log-books will be posted back to the assessor and checked for completion every two months.

Demographic information will also be collected including age, sex, height, weight, profession, sports and leisure activities, medical history, and medication intake. Information about severity and duration of symptoms and previous episodes of shoulder pain are also documented.

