### Interventions

#### Both groups

All participants will undergo a clinical examination process starting with a thorough history taking, followed by a physical examination of the cervical spine, the shoulder girdle, and the shoulder joints. All joints are manually assessed with passive, active, and combined angular movements, and with translatory tests according to the description of Kaltenborn [55], Evjenth and Hamberg [56] or Maitland [57]. Isometric resistance tests are used to judge shoulder strength and pain. Integrity of the rotator cuff is assessed with the external rotation lag sign [58], the lift off test [59], and the hornblowers' sign [60]; involvement of the neural system with upper limb tension tests described by Butler [61]. Contributing factors such as a slouched posture, forward head position, thoracic kyphosis, or protracted shoulders are noted and if necessary also assessed in detail. Results serve as basis for the treatment of participants allocated to the group receiving individualized physiotherapy.

All participants will attend two 20-30 minute contact sessions per week over a 5 week period. Afterwards participants will continue with their home exercises for another 7 weeks. At the beginning of treatment all participants will receive an information booklet containing basic information about anatomy and biomechanics of the shoulder complex, a short description of the aetiology of SIS and the pathology itself, and a brief overview about possible contributing factors to their shoulder pain. The booklet also explains the goals to be achieved with treatment, and it provides general guidelines for behaviour through daily living. Participants will also receive a shoulder log book for documentation of their weekly pain levels, additional treatments or medication, sick leave, and the completion of the home exercise during the intervention phase and during the follow up period. Participants will be requested not to make use of other treatment options and not to change their medication intake during the intervention phase. However, due to ethical considerations the use of analgesics and non-steroidal anti-inflammatory drugs will be permitted and will be recorded in the shoulder log-book.

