Treatment will be administered by experienced physiotherapists with an international qualification for manual therapy (IFOMPT standard). All physiotherapists will be trained prior to commencement of the study to guarantee a uniform background and treatment application. A written manual with detailed and comprehensive instructions is given to the therapists. Thoroughness of the application is supported by structured recording forms and check lists, monthly team meetings and audits.

The two groups are as follows:

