### Follow-up evaluation

Patients are assessed at baseline, after completion of the intervention period at 5 weeks, and at 3 and 12 months after inclusion to assess the long term outcome of the intervention. An overview of the outcome measures is given in Table 3.

**Table 3 T3:** Primary and secondary outcome measures

Primary Outcomes	Measurement	Follow up
Shoulder pain and disability index (SPADI)	13 items (5 for pain, 8 for function) scored on a 100 mm visual analogue scale	baseline; 5 weeks; 3, 12 months

Patients' global impression of change	Ordinal scale (1-much worse, 2-slightly worse, 3-no change, 4-slightly better, 5-much better)	5 weeks; 3, 12 months

**Secondary Outcomes**	**Measurement**	**Follow up**

Generic patient-specific scale	11 point visual numeric rating scale (end descriptors of 0 = impossible to do, 10 = no difficulties at all)	baseline; 5 weeks; 3, 12 months

Average weekly pain score	11 point visual numeric rating scale (end descriptors of 0 = no pain, 10 = worst pain possible)	baseline; 5 weeks; 3 months

Patients' satisfaction with treatment	11 point visual numeric rating scale (end descriptors of 0 = completely dissatisfied, 10 = completely satisfied)	5 weeks

Kinesiophobia/Fear avoidance beliefs	Modified fear avoidance beliefs questionnaire (FABQ)	Baseline

Catastrophizing	Pain catastrophizing scale (PCS)	Baseline

Patients' expectancies of treatment effect	One modified question from the Credibility/Expectancy Questionnaire (CEQ)	Baseline

Compliance	Shoulder log book: Attention of treatment sessions and completion and frequency of home exercises	5 weeks; 3, 12 months

Costs	Cost diary: Disease specific healthcare utilization, days of sick leave, drug use, paid help	5 weeks; 3, 12 months

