### Data analysis

First, descriptive statistics for demographical characteristics of the whole group will be used. Second, descriptive statistics for demographical and clinical characteristics, for baseline results of outcome measures and other potential confounding variables for the intervention group and control group will be used. Differences will be calculated for within-groups results and between-groups comparisons. Results will be calculated according to the "intention-to-treat principle". Between groups-analysis will include differences between baseline and follow up measurements for each clinical outcome measure used, their standard deviations and 95% confidence intervals. Additionally mixed models for the long term follow ups will be used. Influence of baseline differences for outcome measures will be assessed in a multivariable linear regression analysis. Statistical significance is set to p ≤ 0.05, clinical importance will be judged by the lower 95% confidence interval which equals the minimum effect size.

An economic evaluation will compare costs of both treatment options from a societal perspective.

Resources recorded in the shoulder log book will be valued using published prices for medical costs. Costs for over the counter drugs, aids, and paid help will be reported directly by the participants in their log-books.

Productivity costs resulting from loss of paid labor will also be calculated by applying the friction costs method, which limits the period of production loss to the time during the work of the person is not replaced.

Between-group differences in outcomes of mean total costs were analyzed by Student's *t*-tests for unpaired observations.

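### Attended trial sessions and their physiotherapy cost are taken from a posted participant log-book; therapist session counts would remove an avoidable risk of bias

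*Protocol article*

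**What the plan says.** Secondary outcome 7 names the shoulder log-book as the source for "Compliance of participants with treatment including the attended treatment visits out of a maximum of ten and the performance of the given home exercises". Table 3 (Follow-up evaluation) repeats this for compliance: "Shoulder log book: Attention of treatment sessions and completion and frequency of home exercises".

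The same paragraph of secondary outcome 7 takes from the book "direct health care costs including physiotherapy, other health provider visits, diagnostic tests, prescriptions and over the counter medication due to shoulder complaints". Data analysis then states: "Resources recorded in the shoulder log book will be valued using published prices for medical costs". Table 3 calls the cost instrument a cost diary, but both text sections name the log-book. No other source is given for the cost of the trial's own sessions.

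The book is issued to participants: "Participants will also receive a shoulder log book for documentation of their weekly pain levels, additional treatments or medication, sick leave" (Interventions, Both groups). That list goes on to home exercise but does not mention trial sessions. On return, the article says: "Log-books will be posted back to the assessor and checked for completion every two months".

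On the therapists' side, Both groups says: "Thoroughness of the application is supported by structured recording forms and check lists, monthly team meetings and audits". No therapist or clinic record is named as the source for attendance or physiotherapy cost.

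**The concern.** The number of trial sessions attended is something the trial itself delivers and can observe. A diary that the participant holds and posts back measures it only for those who return the diary. Returning a diary and attending sessions both depend on the patient staying engaged, so whether the count is available may be tied to its value. The diary is a natural source for home exercise, outside care, medication, sick leave and paid help, which nobody at the clinic sees. For the clinic's own sessions it is the weaker source.

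Two things are at stake: a listed secondary outcome (compliance) and the trial physiotherapy component of the cost comparison, which is aim (b).

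**Working it through.** **Where the 15% comes from.** The only relevant rate in the article is the drop-out allowance under Sample size (difference 13, SD 20, alpha 0.05, power 80%). Taking alpha as two-sided, n per arm = 2 × (1.960 + 0.842)² × 20² / 13² = 37.1, rounded up to 38. Then 38 / 0.85 = 44.7, rounded up to 45 per arm, or 90 in total. The stated size reproduces. The 15% is therefore an allowance for loss in the SPADI comparison, not a rate of stopping treatment. It serves below only as a stand-in.

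**Planned sessions.** Both groups states: "All participants will attend two 20-30 minute contact sessions per week over a 5 week period". That is 2 × 5 = 10, which matches the maximum of ten in the compliance outcome. The Intervention group section gives six to ten sessions for that arm.

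**Bias in mean attendance.** Let d = share who stop attending, c = mean sessions of the others, v = mean sessions of those who stop, and m = share of the stoppers' books that are missing.

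- True mean = (1 − d)c + dv
- Mean from returned books = [(1 − d)c + d(1 − m)v] / [(1 − d) + d(1 − m)]
- Overstatement = the difference = (c − v) × dm(1 − d) / (1 − dm)

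Assumed, not in the article: c = 9.5, v = 2 to 6, m = 0 to 100%. With d = 15%:

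| m | v = 2 | v = 4 | v = 6 |
|---|---|---|---|
| 0 | 0 | 0 | 0 |
| 50% | 0.52 | 0.38 | 0.24 |
| 100% | 1.125 | 0.825 | 0.525 |

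Example, m = 50% and v = 2: the true mean is 0.85 × 9.5 + 0.15 × 2 = 8.375. Returned books give (8.075 + 0.15) / 0.925 = 8.89. The difference is 0.52.

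Example, m = 100% and v = 2: 9.5 − 8.375 = 1.125.

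With c = 9 and m = 100%, the overstatement is 0.15 × (9 − 6) = 0.45 to 0.15 × (9 − 2) = 1.05. Letting d run from 5% to 25% with c = 9.5 gives a range of 0 to 1.88.

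**Bias in the arm contrast** (c = 9.5, v = 4), as the difference between the two arms' overstatements:

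| d in the two arms | m = 50% | m = 100% |
|---|---|---|
| 15% and 15% | 0.00 | 0.00 |
| 10% and 20% | 0.23 | 0.55 |
| 5% and 25% | 0.46 | 1.10 |

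Example, 10% and 20% with m = 100%: 0.20 × 5.5 − 0.10 × 5.5 = 0.55. The unequal rates are assumptions; nothing in the article suggests them.

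**Timing of the check.** Sessions run over 5 weeks and books are checked every two months. If the first check falls at about two months, all sessions are over, and a gap can be filled only by recall.

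**The case against.** A reader might infer that books go missing for precisely those patients who stop attending, so that attendance is overstated and the cost comparison distorted. The documents do not support that. They give no return rate and do not link non-return to non-attendance. Follow-up runs to 12 months, so a patient counted in the 15% may have attended every session and already posted the pages covering them. The two-monthly check is a partial safeguard. Distortion between arms needs patterns that differ by arm.

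Nor can one infer that patients without a book will be excluded or counted as zero cost. Imputation is a third option, and the handling of missing books may sit in a full protocol or SAP that is not shown. Data analysis commits to intention-to-treat.

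It is also tempting to read the two session statements as a planned difference in resource use between arms. They are an unreconciled inconsistency: ten sessions are stated for all participants, which includes the intervention group.

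Finally, the recording forms are described as supporting thorough application of treatment. The article does not say that they count sessions. It also does not say who enters attendance in the log-book.

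All of this stands, and it limits the point to a risk. It does not remove it. The log-book is a stated choice of instrument rather than a detail left out, and a more direct source is available for the trial's own sessions.

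**Conclusion.** The point holds as an inexpensive improvement, worded as a risk. Attended sessions and the trial physiotherapy cost rest on a posted participant record when the people delivering the sessions could count them. If 15% stop early, the possible overstatement of mean attendance runs from 0 to about 1 session out of 10, depending on how many of their books are missing. Only the 15% is the article's figure, and it is borrowed from another purpose; the other inputs are assumptions. The contrast between arms may be biased if stopping or non-return differs by arm, and is unbiased in visits if the patterns are equal. No size can be put on the bias in cost, because the article gives no prices. The SPADI and global impression outcomes and the sample size of 90 are not touched.

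**What to change.** State in secondary outcome 7, Table 3 and Data analysis that the number of attended trial sessions, for compliance and for the trial physiotherapy component of direct costs, comes from the therapists' session records for every randomised patient. If the forms do not hold a session count, add one. Keep the log-book for home exercise, outside care, medication, sick leave and paid help, and use its session entries only as a cross-check.

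Reconcile the two statements on planned sessions (Both groups; Intervention group), so that it is clear what the maximum of ten refers to in each arm.

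The cost is a short change to the text and entry of a session count for 90 patients. The change does not complete total costs for a patient without a log-book: the other items stay missing and still need their own handling.
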